**Fig. 2 Fig2:**
[figure not shown]
Themes of the program sessions. Each session lasts for about 1.5 h and participants receive a homework assignment which is to be discussed at the subsequent session

### The control

The control condition consists of unrestricted access to CAU. In Sweden, the majority of support to the target group is provided or coordinated via municipalities’ social services, and includes for instance support group activities or individual counselling. In severe cases, children may be referred to the Child and Adolescent Psychiatric Services. Support may also be provided via school health care services and non-profit organizations. In addition, there are a few websites that contain specific information and support for our target group.

### Sample size

The sample size calculation is based on the ability to detect a medium or larger effect size, corresponding to a standardized mean difference (Cohen’s d) of > 0.05 [61]. Based on differences between means, an *a priori* calculation of the estimated sample size, using the G*Power software [62], and accounting for an unequal allocation ratio of 1.8 in favour of the intervention group, reveals that 140 participants need to be included in the trial, 90 in the intervention group and 50 in the control group (power = 0.80, α = 0.05, 2-tailed).

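### The sample size target is printed as Cohen's d > 0.05, but 140 participants give the stated 80% power only at about d = 0.5

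*Protocol article*

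**What the plan says.** The Sample size section of the protocol article bases the calculation on "the ability to detect a medium or larger effect size" and translates this into a number: "corresponding to a standardized mean difference (Cohen’s d) of > 0.05". The calculation is for a difference between two means, was done in G*Power, and is described as "accounting for an unequal allocation ratio of 1.8 in favour of the intervention group". The result is that "140 participants need to be included in the trial, 90 in the intervention group and 50 in the control group", with "power = 0.80, α = 0.05, 2-tailed". The Target sample section repeats the aim of at least 140 participants. No other part of the article gives an effect size or corrects this one.

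**The concern.** The sentence gives the same target in two ways that differ tenfold. By the usual convention a medium standardized difference is 0.5, whereas 0.05 is a trivial one. A trial of 140 people cannot have 80% power for a difference of a twentieth of a standard deviation, so the printed effect size and the printed sample size cannot both be right.

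The figure matters because the whole sample size argument rests on it. The article names four primary instruments (CES-DC, Brief COPE, WHOQOL-BREF and AUDIT-C) and gives no target difference for any of them individually. A reader who takes the number literally would think the trial well powered for very small effects, and could give a non-significant result far more weight against such effects than it deserves. The calculation also cannot be reproduced from the inputs as printed.

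**Working it through.** **Inputs, all from the Sample size section**
- Two-group comparison of means, standardized difference d (so SD = 1)
- α = 0.05, two-sided; power 0.80
- Allocation 1.8 to 1; n₁ = 90 (intervention), n₂ = 50 (control)
- Printed target d = 0.05, with the verbal label medium. The article does not print 0.5; that value is taken from the usual convention and tested below.

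**Step 1. Reproduce the plan's 140.** In the normal approximation the control group size is

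n₂ = (1 + 1/1.8) × (1.960 + 0.842)² / d² ≈ 1.5556 × 7.849 / d² = 12.21 / d²

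- At d = 0.5: 12.21 / 0.25 = 48.8, so 49 control. Then 1.8 × 49 = 88.2, so 89 intervention. Total 138.
- With the noncentral t distribution, which G*Power uses, the unrounded solution at d = 0.5 is 49.5 + 89.2 = 138.7. Rounding each arm up gives 50 + 90 = **140**, the plan's figure exactly.

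**Step 2. Try the printed effect.** At d = 0.05:
- 12.21 / 0.0025 gives 4,884 control. Then 1.8 × 4,884 = 8,791.2, so 8,792 intervention. Total **13,676** (13,678 with the noncentral t).
- That is 13,676 / 140 ≈ 98 times the stated sample size. A one-sided test would still need 10,772.

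**Step 3. Power with 90 and 50.** The noncentrality parameter is d × √(90 × 50 / 140) = d × 5.669, with 90 + 50 − 2 = 138 degrees of freedom.

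| d | Noncentrality | Two-sided power |
|---|---|---|
| 0.05 | 0.283 | 0.059 |
| 0.5 | 2.835 | 0.804 |

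Power at the printed effect is thus barely above the 5% type I error rate.

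**Step 4. Smallest effect with 80% power.** Solving the noncentral t power for d at 90 and 50 gives d = **0.498**. The normal approximation gives (1.960 + 0.842) × √(1/50 + 1/90) = 0.494. Either way it is about ten times the printed 0.05.

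**The case against.** The strongest reply is that this is a misprint and not a design error. The same sentence calls the effect medium, and the printed sample size, ratio, α, power and sidedness all reproduce at d = 0.5, so the calculation was evidently run with 0.5. On that view the figure of some 13,700 participants only dramatizes a slipped decimal, since the sample size, conduct and analysis stay as they are. The Analyses section contains no equivalence or futility rule, so nothing in the plan would formally rule out effects as small as 0.05. Even a correctly stated 80% power would not let a non-significant test rule out the design effect.

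Much of this stands. A misplaced decimal is the most plausible origin, 140 is the right number for d = 0.5, and over-reading of a null result is a risk and not a planned inference. None of it makes the printed number correct. The greater-than sign does not help, because the power claim fails over the whole range from 0.05 to just under 0.50. Nor is 0.05 a stray significance level, as α is stated separately. A reader may guess the intended value, but the only numerical target in the article is still wrong.

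**Conclusion.** The figure is wrong as written. The printed target is one tenth of the effect that the stated design can detect: power at d = 0.05 is 0.059 against the claimed 0.80, and 80% power is reached only at d of about 0.50. The sample size of 140 is consistent with d = 0.5 and is not itself in error on this point.

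The result rests on the article's own test, α, power, ratio and arm sizes. That the intended value was 0.5 is an inference from the word medium and from the exact match at 90 + 50; the original software input is not shown. The power of 0.804 applies to a single two-group comparison of means with data from all 140 participants. The calculation states no allowance for dropout. For illustration, if an equal share of each arm were lost and only the remaining participants were analysed, power at d = 0.5 would be 0.761 with 10% lost, 0.710 with 20% and 0.651 with 30%.

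**What to change.** Check the effect size entered in the original G*Power calculation and, if it was 0.5, replace the printed value with a Cohen's d of 0.5. Add one sentence stating that 90 and 50 participants give 80% power for d of about 0.50 or more, for one two-group comparison of means with all 140 analysed, and that smaller effects are not covered at that power. If the registry record or the full protocol carries the same figure, correct it there too; neither was available to check.

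The cost is one corrected number and one added sentence. Recruitment, allocation, sample size and analysis do not change.

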### The target sample

The aim is to include at least 140 adolescents (aged 15–25 years) who perceive at least one parent to have a substance use problem and/or mental illness. Additional inclusion criteria (Fig. 1) are as follows: having access to a device, such as a computer or tablet with internet access, being fluent in Swedish, and having consented to participate. Participants who reveal symptoms of severe depression or show indications of either suicidal or self-injurious behaviour will be excluded from the study and referred to appropriate care.

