### Assessment

The assessments for this study will consist of a baseline measurement (t0), which will take place before randomization, and three follow-up measurements after six (t1), 12 (t2), and 24 months (t3). Participants will be invited to each assessment by e-mail, and if necessary up to three reminders will be sent at five, ten, and 15 days after the first invitation, respectively. All assessments will be in the form of an online survey distributed via the survey data collection tool Easyresearch (QuestBack, Norway). In order to increase the response rate, participants will be offered an incentive of one cinema gift certificate, corresponding to approximately 11 Euros, for each assessment. The resulting survey contains 216 questions and takes approximately 30 min to complete.

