### Analyses

#### The effectiveness study

Data will be analysed according to the intention-to-treat (ITT) principle, accounting for all included participants regardless of whether or not they have responded to the follow-up assessments. Missing data will be handled using the Missing Value Analysis routine in the SPSS software (IBM SPSS Statistics 23, IBM Corporation, NY, USA).

Data analyses will consist of comparing outcome measurements at baseline (t0) and subsequent follow-up (t1, t2, and t3) assessments, with regards to within-group and between-group comparisons.

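### The target of 140 is the number needed with complete outcome data, but it is used as the number to include, with no allowance for the non-response the protocol anticipates

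*Protocol article*

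**What the plan says.** The Sample size section of the protocol article describes one calculation: "Based on differences between means, an *a priori* calculation of the estimated sample size, using the G*Power software", "accounting for an unequal allocation ratio of 1.8 in favour of the intervention group", with "power = 0.80, α = 0.05, 2-tailed". Its result is that the software "reveals that 140 participants need to be included in the trial, 90 in the intervention group and 50 in the control group". The effect size is described as medium or larger but printed as "corresponding to a standardized mean difference (Cohen’s d) of > 0.05".

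The target sample section uses the same figure for recruitment: "The aim is to include at least 140 adolescents (aged 15–25 years". Neither section mentions a margin for loss to follow-up.

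Other sections foresee incomplete response. Under Assessment, follow-up is by e-mailed online survey of 216 questions at 6, 12 and 24 months, with up to three reminders per round, and "In order to increase the response rate, participants will be offered an incentive". The effectiveness study section plans an intention-to-treat analysis "accounting for all included participants regardless of whether or not they have responded to the follow-up assessments", with missing data handled by the SPSS Missing Value Analysis routine.

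**The concern.** A two-means calculation returns the number of participants who must contribute an outcome value. The protocol presents that number as the one to include. The two are equal only if everyone included responds, and the protocol's own follow-up and analysis arrangements show that full response is not expected.

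What is at stake is how the 80% figure is read. A reader of the results would take the trial to have had 80% power against a medium effect at whichever follow-up is reported. If a sizeable share of outcomes is missing, the power of the comparison on which the calculation rests is lower, and a non-significant difference says less about a medium effect than the protocol suggests.

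**Working it through.** **Inputs.** From the Sample size section: power 0.80, two-sided alpha 0.05, allocation ratio 1.8, 90 intervention and 50 control, comparison of two means. The effect size is read as d = 0.5. The printed 0.05 cannot be the value used: by the normal approximation it would need 4,884 participants in the control arm alone, and 140 participants would have about 6% power. The loss rates below (5% to 40%, equal in both arms) are assumptions, because the protocol gives none.

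**Formula.** Two-sample t-test with n1 and n2 participants:
- degrees of freedom = n1 + n2 − 2
- noncentrality = d × √(n1 × n2 / (n1 + n2))
- power = probability that a noncentral t with these values exceeds the two-sided 5% critical value

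**Step 1: reproduce 140.** With n1 = 90, n2 = 50 and d = 0.5, noncentrality = 0.5 × √(4500/140) = 2.835 on 138 degrees of freedom, critical value 1.977, power 0.804. Stepping up the control arm and rounding 1.8 times it for the intervention arm, 50 + 90 is the first design to reach 0.80. The one-sided version gives 112 and does not fit. So 140 is the complete-data requirement, with no hidden allowance.

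**Step 2: the first few losses.**
- 89 vs 50: 0.802
- 88 vs 50: 0.8005
- 87 vs 50: 0.799
- 90 vs 49: 0.799

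One or two missing participants make no practical difference.

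**Step 3: a range of loss.** Put n1 = 90(1 − a) and n2 = 50(1 − a) into the same formula. For the last column, solve for the d that gives power 0.80.

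| Loss a | With data (intervention / control) | Power at d = 0.5 | d detectable with 80% power |
|---|---|---|---|
| 0% | 90 / 50 | 0.80 | 0.50 |
| 5% | 85.5 / 47.5 | 0.78 | 0.51 |
| 10% | 81 / 45 | 0.76 | 0.52 |
| 20% | 72 / 40 | 0.71 | 0.56 |
| 30% | 63 / 35 | 0.65 | 0.60 |
| 40% | 54 / 30 | 0.58 | 0.65 |

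As an example, at 30% loss noncentrality = 0.5 × √(63 × 35 / 98) = 0.5 × √22.5 = 2.372 on 96 degrees of freedom, power 0.651.

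**Step 4: what baseline adjustment could give back.** If the analysis adjusts for the baseline value and the baseline–outcome correlation is r, the effective effect size is d/√(1 − r²). For r = 0.5 this is 0.5/√0.75 = 0.577; for r = 0.6 it is 0.5/0.8 = 0.625. The values of r are assumptions too.

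| Loss | Power, r = 0.5 | Power, r = 0.6 |
|---|---|---|
| 20% | 0.83 | 0.88 |
| 30% | 0.77 | 0.84 |
| 40% | 0.71 | 0.77 |

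**The case against.** Several points on the other side have force.

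- **No sum is wrong.** This stands. At d = 0.5 the calculation is correct and gives 140. The fault lies in the use made of the figure.
- **An article condenses the full protocol, where a dropout assumption might sit.** This would answer a complaint about silence. Here the article prints the whole calculation and equates its output with the number to include, so the claim it makes can be checked as it stands.
- **The target is a minimum.** True, and more than 140 could be recruited, but no higher target is stated and 0.80 is attached to 140.
- **The missing-data routine and earlier survey rounds recover information.** Partly right. Keeping everyone in an intention-to-treat analysis does not in itself replace unobserved outcomes, but a model that uses baseline and earlier follow-ups can recover some of what is lost. The article does not detail the routine, so the amount is unknown.
- **Baseline adjustment may cover the loss.** It can. A correlation of about 0.31, 0.45, 0.55 or 0.64 would hold power at 0.80 for 10%, 20%, 30% or 40% loss. The calculation is not based on such an analysis, however, and the effectiveness study section names none.

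A reader might infer that the stated power fails as soon as anyone does not respond, or that it assumes complete data through 24 months. The documents support neither. Power is still at least 0.80 after two intervention losses, and the Sample size section describes one comparison without naming a follow-up. Nor can it be said that the trial as finally analysed will be underpowered, since neither the loss rate nor the analysis model is given.

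**Conclusion.** The point holds in a limited form. The 140 is the requirement with complete data, it doubles as the inclusion target, and nothing is set aside for the non-response the protocol prepares for. The 0.80 therefore describes 140 participants with outcomes rather than 140 included.

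The shortfall is negligible for one or two losses, becomes material at about 5–10%, and would bring power to roughly two in three at 30%. That size rests on four assumptions: the effect size is a misprint for 0.5, the test is the unadjusted comparison of means used for planning, loss is equal in both arms, and the rates are illustrative. An adjusted analysis could remove part or all of the deficit. The relabelling is firmly supported; the size of the shortfall can only be given as a range.

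**What to change.** In the Sample size section, describe 90 and 50 as the numbers with outcome data, and correct or confirm the printed effect size. Then state power and detectable effect for 140 randomised under a declared attrition assumption at a named follow-up. For example, with 30% loss (63 versus 35 with data), the unadjusted comparison has power 0.65 for d = 0.5, and the effect detectable with 80% power is 0.60.

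If the analysis will adjust for baseline, name that analysis and give its power with the assumed correlation: at 30% loss, 0.77 for r = 0.5 and 0.84 for r = 0.6.

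The cost is a sentence or two and no extra enrolment. The downside is that the stated power will look less favourable.

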### Outcome measurements

#### Primary outcomes

To measure depressive symptoms during the preceding week, the Center for Epidemiological Studies Depression Scale for Children (CES-DC) will be used [47]. This scale consists of 20 items with response options on a four-point Likert scale. It measures depressive symptoms during the preceding week and is a valid measure of general childhood psychopathology [48]. The scale has shown high internal consistency (α = 0.91) and has been proven to be valid among Swedish adolescents when compared with the Beck’s Depression Inventory (*r* = 0.81) [49].

Participants’ coping strategies will be measured using the Brief COPE, which consists of 28 items using four-point Likert scales and has been proven to have acceptable high internal consistency (α = 0.58–0.92) [50, 51].

To measure quality of life, the World Health Organization’s Quality of Life Questionnaire (WHOQOL-BREF) will be used. The scale contains 26 items using five-point Likert scales and measures quality of life in four principal domains: physical health, mental health, social relations, and environment [52]. This instrument has demonstrated good to excellent psychometric properties with Cronbachs’s α ranging from 0.68 to 0.82, and construct validity (item-total correlations) with r ranging from 0.45 to 0.70 [53].

Alcohol consumption will be assessed using the short version of the Alcohol Use Disorders Identification Test (AUDIT-C) [54], assessing frequency of drinking, quantity consumed, and frequency of heavy episodic drinking (i.e., binge drinking). The instrument has shown satisfactory internal consistency (α = 0.80) and good validity (AUROC = 0.85) [55].

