### Implications for practice

Studies have revealed that the majority of children whose parents have substance use or mental health problems do not receiving existing support. In addition to problems with identifying individuals and recruiting them to available intervention programs, a related issue is how to make face-to-face intervention available in rural areas. This has been an issue raised among professionals working in the rural northern part of Sweden and a web-based solution has been requested. Thus, there is an urgent need to develop and evaluate novel intervention programs, such as web-based interventions, and disseminate successful programs to a broader audience. If this study demonstrates sufficient effectiveness in *Grubbel*, our aim is to implement and disseminate the intervention throughout Sweden, which will be a cost-effective means to provide support. This study therefore makes an important contribution, not only to this field of research but also to agencies, authorities, and organisations that provide support to this target group.

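### Four unranked primary outcomes at three follow-ups are paired with a sample size that fits a single test, so the stated alpha of 0.05 and power of 0.80 hold together only for a lead comparison the article never names

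*Protocol article*

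**What the plan says.** Under Primary outcomes the Protocol article describes four instruments in turn, with no order among them: the CES-DC for depressive symptoms, the Brief COPE, the WHOQOL-BREF, which "measures quality of life in four principal domains: physical health, mental health, social relations, and environment", and a fourth: "Alcohol consumption will be assessed using the short version of the Alcohol Use Disorders Identification Test (AUDIT-C"). The Assessment section sets "three follow-up measurements after six (t1), 12 (t2), and 24 months (t3"). The Analyses section has outcomes compared at baseline and all three follow-ups, within and between groups. No follow-up is named as the main one.

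The Sample size section makes one calculation, for a difference between means. It is "based on the ability to detect a medium or larger effect size", "corresponding to a standardized mean difference (Cohen’s d) of > 0.05", "accounting for an unequal allocation ratio of 1.8 in favour of the intervention group". The result is 140 participants, 90 and 50, with "power = 0.80, α = 0.05, 2-tailed".

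Under Implications for practice, dissemination throughout Sweden depends on the result: "If this study demonstrates sufficient effectiveness in" *Grubbel*. The article does not define what counts as sufficient.

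**The concern.** Which outcomes are primary and what the sample size supports are both decisions that the article itself makes, and they do not fit each other. One alpha and one power are given for one comparison of means. Four outcomes hold equal primary status, and each has three candidate time points.

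At stake is what a positive trial would mean. With no lead outcome or time point, the lead result could be chosen after the data are seen, and the reader could not tell which error rate applies to it. If the choice is instead disciplined by an adjustment, or by requiring success on all four, 140 participants no longer give each outcome, or the joint claim, the stated power.

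**Working it through.** **Inputs from the article:** 90 and 50 participants, two-sided alpha 0.05, power 0.80, four primary instruments, three follow-ups. **Assumed:** d = 0.5; all 140 analysed; correlations of 0 to 0.7 between outcomes and 0.5 to 0.7 over time (the article gives none); one score per instrument; between-group tests only.

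**1. Reproducing 140.** For a two-sample t-test the noncentrality is d × √(n₁n₂/(n₁+n₂)) = 0.5 × √(90 × 50/140) = 2.835 on 138 degrees of freedom. Two-sided power at 0.05 is 0.804, and the smallest sample at ratio 1.8 that reaches 0.80 is 50 + 90 = 140, an exact match. With the printed d = 0.05, about 13,676 participants would be needed (normal approximation), and 140 would give power of only about 0.05 to 0.06. So 140 is one two-sided test at 0.05 with d = 0.5 and no allowance for further primaries.

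**2. If any one significant primary suffices, unadjusted.** With k independent tests the chance of at least one false positive is 1 − 0.95^k. For k = 4 this is 0.185; for k = 4 × 3 = 12 it is 0.460. With correlated test statistics (multivariate normal simulation):

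| Correlation between outcomes | Correlation over time | Four outcomes, one time point | Four outcomes, three time points |
|---|---|---|---|
| 0 | 0.5 | 0.185 | about 0.41 |
| 0.3 | 0.5 | 0.174 | 0.393 |
| 0.5 | 0.5 | 0.156 | 0.354 |
| 0.5 | 0.7 | 0.155 | 0.314 |
| 0.7 | 0.7 | 0.130 | 0.265 |

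The time correlation does not affect the one-time-point column.

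**3. If alpha is split over four.** 0.05/4 = 0.0125. With 90 and 50, power at d = 0.5 is 0.620, and the effect detectable with power 0.80 is d = 0.596. Restoring 0.80 would take 199 participants (128 + 71).

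**4. If all four must succeed at one time point.** Alpha stays at or below 0.05. Power if independent is 0.804⁴ ≈ 0.42 (t-test), or 0.809⁴ ≈ 0.43 with the normal approximation. At an outcome correlation of 0.7 it rises to about 0.64.

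**5. Holm over four, one time point.** 0.62 is the power at the first step and so a floor for each outcome. If all four true effects are d = 0.5, average power per outcome is about 0.71 to 0.74, and the chance of at least one rejection is about 0.83 to 0.98 (normal approximation, correlations 0 to 0.7).

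**The case against.** The strongest reply is that the article gives no success rule. A reader might infer that any of twelve between-group tests may be declared a positive primary result, and so that the true error rate is several times the stated one. The text does not say that. The hypothesis under Objective and research questions is a list joined by *and*, and a conjunctive rule would protect alpha. That list cannot serve as the rule as it stands, though, because it includes behavioural problems, which the YSR measures as a secondary outcome. The count of twelve is also inferred: one longitudinal model per outcome with a single group-by-time test would fit the Analyses section and give four tests.

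A reader might also infer that subscales will be tested. The four WHOQOL-BREF domains, and the range of alphas quoted for the Brief COPE, suggest it, but the article does not state it. The point does not use it.

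Multiplicity rules and scoring are commonly left to a statistical analysis plan, and one may exist, so their absence is not the finding. It can further be argued that 0.05 and 0.80 are correct for any single comparison with complete data and d = 0.5, that distinct constructs may each be tested at 0.05, and that Holm would give power above 0.80 for at least one success if all four effects were 0.5.

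All this stands as a limit on the error-rate figures. It does not remove the mismatch. The last argument needs a medium effect on all four outcomes, which the sample size section does not assume. Separate claims at 0.05 would still need one time point each, and would not give a 5% error rate for an overall claim of effectiveness.

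**Conclusion.** The point holds as a mismatch between two things the article fixes: four equal primaries over three follow-ups, and a sample size for one test. Alpha 0.05 and power 0.80 hold together for a single lead outcome and time point, or for the first test in a fixed order. The article names neither.

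The cost depends on the rule eventually used:
- any one suffices, unadjusted: false-positive risk about 0.13 to 0.19 at one time point, and about 0.27 to 0.41 over three (0.46 if all twelve are independent);
- alpha split over four: power 0.62 per outcome, detectable d about 0.60;
- all four required: power about 0.43 if independent, about 0.64 at correlation 0.7.

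These rest on d = 0.5, complete data and assumed correlations. The first line also rests on a success rule that the article does not state, so it is a conditional risk and not a property of the plan as written.

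**What to change.** Before any follow-up data are analysed, name one primary score at one primary time point, tested two-sided at 0.05 (for example the CES-DC total at one fixed follow-up). Make the other outcomes and time points secondary. The existing 140 then matches its stated power, given d = 0.5 and complete data.

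If all four instruments must stay primary, fix one score for each and one common time point, apply Holm over the four, and restate power at d = 0.5 as at least about 0.62 per outcome. Note that 0.62 is the first-step floor and that the average is higher if several effects are real.

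In either case, correct or explain the printed effect size so that the calculation can be followed.

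The cost is an amendment and matching registry wording. Either three instruments lose primary status or the stated power falls. No extra participants are needed. The change must come before the follow-up analysis, because a lead outcome named afterwards would not be credible.
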